#### 2.3.2. NYHA, CCS and SF-36

*Angina pectoris* and exertional dyspnea, the two central symptoms of IHD, will be graded pre- and postoperatively at the three-month follow-up using the standardized classifications systems from the Canadian Cardiovascular Society (CCS) and New York Heart Association (NYHA) [91]. Further, the 36-Item Short Form Health Survey (SF-36) is used to assess subjective participant morbidity [92].

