#### 2.3.4. Echocardiography, 3-Month Control Visit, and Follow-Up Period

As the development of more sophisticated echocardiographic techniques has revolutionized the field of cardiology and cardiac surgery by offering relevant dynamic insights to both cardiac anatomy and function, IHD-EPITRAN will assess all participants in all cohorts with transthoracic echocardiography (TTE). Critically, the non-IHD control patients in cohort IV will also undergo TTE recording. In this way, valuable functional reference values are obtained.

The TTE recordings will be performed with prespecified acquisition methods by designated cardiologists [94]. The TTE recordings will include both anatomical and functional assessments of atria, valves, and ventricles as well as recording the presence or absence of pericardial effusion, thrombus, and aneurysm. Moreover, the echocardiographic raw data will be exported and stored for further analyses, such as strain and strain rate measurements.

In addition, the 3-month follow-up visit includes a morbidity evaluation with the use of CCS and NYHA and SF-36 questionnaires (Section 2.3.2) alongside routine clinical anamnesis and status. Moreover, the CABG cohort II will undergo ankle-brachial indexing (ABI) to record any asymptomatic peripheral artery disease (PAD).

A six-month prospective follow-up period starting from recruitment will be incorporated. Additionally, a six-month retrospective evaluation will be performed preceding the moment of recruitment. Hospital admission rates with primary cause(s), medication changes, determination of Major Adverse Cardiac and Cerebrovascular Events (MACCE), and all-cause mortality for follow-up make up the parameters assessed both during retrospective evaluation and prospective follow-up.

Hospital admissions regarded as cardiovascular-based will be recorded using the International Statistical Classification of Diseases and Related Health Problems (ICD-10). The IHD-EPITRAN study will use a modified MACCE definition adopted from the ITALIC trial [95] with a composite primary outcome including cardiovascular death, MI, acute revascularization, stroke, transient ischemic attack (TIA), major bleeding (The Bleeding Academic Research Consortium [BARC] classes 3–5), or other hospitalization due to ischemic cardiovascular cause [96].

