All-cause mortality with the ICD-10 codes for both underlying and immediate causes of death from the death certificates from the six-month follow-up will be documented with a focus on deaths considered as cardiovascular-related. Cardiovascular medication changes with ATC codes and DDDs will be recorded and analyzed with InnoLIMS^®^ Medical or equivalent software (Section 2.3.1). The medication data yielded will subsequently be used to model either an improved (reduced medication or dosage) or worsened (added medication or increased dosage) disease state.

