**Study cohort IV, patients screened negative for IHD with coronary computed tomography**	
Any prior cardiovascular disease or medication currently or in history	As critical non-IHD controls, the aim is to also recruit patients that represent overall “cardiovascular health”

**Table 3 ijms-22-06630-t003:** Planned outcomes of the IHD-EPITRAN study. Outcome 1 and outcomes 2–5 encase inter- and intra-cohort comparisons, respectively. Morbidity parameters: Section 2.3.2. *A-to-I*, adenosine-to-inosine; *AVR*, aortic valve replacement (III); *AVS*, aortic valve stenosis; *CABG*, coronary artery bypass grafting (II); *CCTA*, coronary computed tomography angiogram (IV); *m^6^A*, N^6^-methyladenosine; *IR*, ischemia-reperfusion; *PCI*, percutaneous coronary intervention; *STEMI*, ST-elevation MI (I).

Primary	Secondary
1. Study sample m6A and A-to-I profiles from the recruitment stage associating with IHD and AVS pathophysiology 1.1. Acute IR controlled for stable ishcemia, pressure overload, and homeostasis (I vs. II-III-IV) 1.2. Stable ishcemia controlled for acute IR, pressure overload, and homeostasis (II vs. I-III-IV) 1.3. Acute IR controlled for homeostasis (I vs. IV) 1.4. Pressure overload controlled for acute IR, stable ishcemia, and hemeostasis (III vs. I-II-IV)	4. Changes in the study sample m^6^A and A-to-I profiles (Recruitment vs. 3-months) associating to 4.1 Therapy effects on Pathophysiology at 3-month follow-up 4.1.1. STEMI-PCI effects (Resolution and relievement acute IR, remodelingl I vs. I) 4.1.2. IHD-CABG effects (Relievement of stable ischemia, remodeling; II vs III) 4.1.3. AVS-AVR effects (Relievement of pressure overload, remodeling; III vs. III) 4.2 All-cause mortality during 3-month follow-up 4.3 Beneficial/adverse/no-response for therapy as measured via echocardiography at 3 months 4.4 Surrogate (non-)metabolite CVD biomarker levels at recruitment, 3 months, changes between
2. Study sample m^6^A and A-to-I profiles from the recruitment stage associating with 3-moth follow-up clinicial parmeters 2.1. Cardiovascular mortality 2.2 Cardiovascular morbidity 2.3. MACCE 2.4 Cardiovascular medication increases or reductions	5. study sample m^6^A and A-to-I profiles from the recruitment stage as in outcomes 4.2.–4.5.
3. Changes in the sample m^6^A and A-to-I profiles (recruitment vs. 3-months) as in outcome 2	6. Study sample quantitative alterations in other RNA modifications as in outcomes 1–5 (2.3.8.)

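### Table 3 ties event outcomes to 3 months although Section 2.3.4 follows them for six; the change-based mortality outcomes cannot be analysed, and cardiovascular death alone has very low power

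*Protocol article*

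**What the plan says.** Section 2.3.4 defines the clinical follow-up: "A six-month prospective follow-up period starting from recruitment will be incorporated". What is assessed in it is listed as "Hospital admission rates with primary cause(s), medication changes, determination of Major Adverse Cardiac and Cerebrovascular Events (MACCE), and all-cause mortality for follow-up". On deaths, the same section says that causes are taken "from the death certificates from the six-month follow-up will be documented with a focus on deaths considered as cardiovascular-related".

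Table 3 uses a different window for the same variables. Primary outcome 2 covers "profiles from the recruitment stage associating with 3-moth follow-up clinicial parmeters", with components "2.1. Cardiovascular mortality 2.2 Cardiovascular morbidity 2.3. MACCE 2.4 Cardiovascular medication increases or reductions". Primary outcome 3 takes the recruitment-to-3-month change in profile and relates it to the outcome 2 list. Secondary outcome 4 also uses that change and includes "4.2 All-cause mortality during 3-month follow-up". Outcome 5 repeats the later items of outcome 4, including that one, with the recruitment sample.

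The Table 3 caption makes outcomes 2-5 intra-cohort and refers to Section 2.3.2 for the morbidity parameters. There, symptoms "will be graded pre- and postoperatively at the three-month follow-up". Section 2.2 sets 50 patients per cohort as a first target. The only power statement (Section 2.4) is 0.95 with 44 per cohort.

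**The concern.** The article gives two windows for the same primary variables. If Table 3 governs, deaths, MACCE and medication changes in months 3-6 are collected but feed no listed outcome, in a study where such events will be scarce.

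The 3-month window also fails logically where the predictor is itself a change measured at 3 months: the patients who die are those without the second measurement.

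Finally, 2.1 makes cardiovascular death a primary sub-outcome inside cohorts of 50. Table 2 excludes complicated infarction, cardiogenic shock and acute heart failure (cohort I), LVEF below 25%, prior open-heart surgery and, in cohort IV, any cardiovascular disease. The stated power of 0.95 does not describe that comparison.

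**Working it through.** **1. Windows side by side**

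| Variable | Collected (Sections 2.3.2, 2.3.4) | Analysed (Table 3) |
|---|---|---|
| Cardiovascular death | six months | 2.1, and 3 by reference: 3 months |
| MACCE | six months | 2.3, and 3: 3 months |
| Medication changes | six months | 2.4, and 3: 3 months |
| All-cause death | six months | 4.2, and 5 by reference: 3 months |
| NYHA/CCS/SF-36 | 3-month visit | 2.2: 3 months (consistent) |

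Only the last row matches. Using six months instead of three gives about 2.0 times the events under a constant hazard. If 70% of events fall in the first three months, it gives 1/0.7 = 1.4 times. Both are assumptions.

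**2. Change-based mortality outcomes**

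The predictor in outcomes 3 and 4 is the 3-month profile minus the recruitment profile. For 2.1 (under outcome 3) and 4.2, the event is death before 3 months. A patient with the event has no 3-month sample, so no death enters the analysis, whatever the death rate. Months 3-6 are the only follow-up described in Section 2.3.4 in which the change can precede a death. Cohort IV is sampled once (Section 2.3.5) and cannot contribute.

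**3. Reproducing the stated power**

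Inputs (Section 2.4): FDR 0.05, 20,000 genes, 1500 prognostic, fold change 2, mean count 10, dispersion 0.43.

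- Per-gene threshold: 0.95 × 1500 × 0.05 / (18,500 × 0.95) = 0.00405.
- Variance of the log fold change per patient pair: (1/10 + 0.43) + (1/20 + 0.43) = 0.53 + 0.48 = 1.01.
- Two-sided Wald test: n = (2.874 + 1.645)² × 1.01 / (ln 2)² = 42.9, so 43. Power at 44 is 0.956.
- An exact negative-binomial test gives 0.949 at 43 and 0.954 at 44.

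The stated 44 reproduces. It describes 44 against 44, which is the outcome 1 setting.

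**4. Same inputs for outcome 2.1**

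With k deaths and 50 − k survivors, the standard error is √(0.53/(50 − k) + 0.48/k), and power is Φ(ln 2/SE − 2.874). For k = 1, SE = √(0.53/49 + 0.48) = 0.701 and power = Φ(0.989 − 2.874) = 0.030.

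| Deaths in 50 | 1 | 2 | 3 | 5 | 10 | 25 |
|---|---|---|---|---|---|---|
| Power | 3% | 7% | 12% | 22% | 47% | 72% |

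Even an even split stays below 0.95. Holding the threshold at 0.00405 favours the plan: recomputing it for the lower power gives about 6% with 5 deaths. The normal approximation is rough at one or two deaths, so these are orders of magnitude.

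**5. Expected deaths**

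The article gives no death rate, so the risk is assumed.

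| 3-month risk | Expected deaths in 50, 3 months | Expected deaths in 50, six months (constant hazard) |
|---|---|---|
| 0.5% | 0.25 | 0.5 |
| 1% | 0.5 | 1.0 |
| 2% | 1.0 | 2.0 |
| 4% | 2.0 | 50 × (1 − 0.96²) = 3.9 |
| 10% | 5.0 | 9.5 |

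At 1% and 2%, the chance of no death at all in a cohort by 3 months is 61% and 36%.

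**The case against.** Collecting data for longer than one outcome's window is not in itself an error, and 3 months matches the visit, the echocardiogram and the second sample. Figure 5D, the timeline of prospective comparisons, is not shown. Sections 2.6 and 4 leave much of the prognostic aim to long-term extensions. Section 2.2 calls 50 per cohort a first target. Cardiovascular death is one of four components of outcome 2 and already part of MACCE.

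Much of this limits how strongly the point can be put. A reader might infer that months 3-6 will be thrown away; the article does not say so, only that no listed outcome in the text uses them. The match with the visit justifies 3 months for 2.2 and echocardiography, but not for deaths, MACCE and medication changes, for which Section 2.3.4 sets six. Enlargement is foreseen without a size, and pooling 200 patients would still give only about 25% power with 5 deaths and 58% with 10.

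A reader might also infer that 2.1 is bound to be null, or that some minimum such as five deaths is required, because the smallest two-sided rank p-value, 2/C(50, k), exceeds 0.05/20,000 = 2.5e-6 for up to four deaths. The documents do not support this:

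- Benjamini-Hochberg is a step-up procedure. The floors of 8.7e-6 (4 deaths), 1.0e-4 (3) and 0.0016 (2) can pass if 4, 41 or 654 features reach them together, and the protocol plans on 1500 prognostic genes.
- The protocol does not choose a rank or permutation test.
- Section 2.3.8 quantifies only eight modifications, where the first step is 0.05/8 = 0.00625, which two deaths can meet.

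Low power is supported; impossibility is not. The futility argument also does not extend to MACCE or medication changes, which may be frequent.

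**Conclusion.** The point holds in three parts of different strength.

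- **Window:** the conflict between Table 3 and Section 2.3.4 is explicit and needs no assumption. The size of the gain does: roughly 1.4 to 2.0 times the events.
- **Change-based mortality:** relating the 3-month change to death within 3 months (outcome 3 through 2.1, and 4.2) is impossible by definition.
- **Cardiovascular death alone:** 2.1 cannot be expected to give a result. This rests on an assumed death rate, the article's own power inputs and intra-cohort analysis of 50. At 1-4% risk power is about 3-7% with one or two deaths. It is still only 22% with the 5 deaths expected at 10% risk. Six months repairs the window but not 2.1: at 1-4% it brings about 1 to 4 deaths.

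This should be corrected. It does not affect outcome 1, to which the stated power applies.

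**What to change.** 1. Reconcile Table 3 with Section 2.3.4: use the six-month window for the event outcomes based on the recruitment sample (2.1, 2.3, 2.4 and the mortality part of 5).
2. Keep NYHA, CCS and SF-36 morbidity (2.2) and echocardiography at 3 months.
3. For the event parts of outcome 3 and for 4.2, set a landmark at the 3-month sample. Include patients who are alive with both samples, and count only events from month 3 to month 6. This makes the mortality analyses definable, though not well powered.
4. Report cardiovascular death alone descriptively and keep it as a MACCE component.
5. Analysing MACCE across cohorts I-III, stratified by cohort, is optional. It would depart from the stated intra-cohort design.

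No new visit, sample or data item is needed. The cost is a documented change to the outcome definitions of a registered study that had enrolled 40 patients at submission, a check of outcomes 6-9, which refer back to 1-5, and the loss of primary status for one sub-outcome.

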**Strengths**
1. Interdisciplinary collaboration enables simultaneous recruitment, sample handling and measurements.
2. A relevant IHD vs. non-IHD comparison is incorporated with a follow-up dimension as well.
3. Coronary artery status is visualized from all participants recruited.
4. Cardiac function is assessed by TTE from all participants recruited.
5. Exclusion of patients with prior clinically relevant manifestations of atherosclerosis than IHD.
6. Participants are surveyed for vascular claudication. ABI for the cohort II to record any asymptomatic PAD.
7. Cohort morbidity an dother background characteristics are meticulously registered, assessed and reported.
8. Study sample collection is designed to minimize the timespan for RNA vulnerable for degradation.
9. Sample use is optimized for as comprehensive measurements as possible. RNA is fractionated for analyses.
**Limitations and management consideration**
1. Coronary evaluation is non-uniform across cohorts. *SYNTAX with ICA for complexity assesment of IHD. The CCTA cohort IV is a primary non-IHD control.*
2. Complete rule out of the effects of systemic atherosclerosis cannot be achieved *Most earlier manifestations of systemic atherosclerosis lead to exclusion, vascular claudication is surveyed (exclusion criterion) and ABI is measure from CABG cohort to record any asymptomatic PAD.*
3. Limited possiblity to adjust medication effects (cohort IV has neither any CVD pathology nor medication). *ATC and DDT alterations are recorded and reported. Immunomodulatry, edication leads to exclusion.*
4. Limited ability to pinpoint precise origins of the forthecoming epitranscriptomic alterations. *Buffy coat leukpcytes can be used for validation, plasma cfRNA is principally derived from EVs.*
5. Incapability to identify biomarkers directly for subclinical IHD due to required cohort morbidity. *(1) Current study assesses the harnessing potential of epitranscriptomics for a source of IHD biomarkers* *(2) Long-term follow-up of cohort IV can address the task.*

## Data Availability

Not applicable (however, see Section 2.4).
